**Methods:**

The study will be conducted in about 35 sites in Germany. Patients with hypercapnic AECOPD with respiratory acidosis (pH < 7.35) will be randomized 1:1 to NIV or NHF. The primary outcome is the combined endpoint of intubation, treatment failure or death at 72 h. The switch from one to the other device marks a device failure but acts as a rescue treatment in absence of intubation criteria. A sample size of 720 was calculated to have 80% power for showing that NHF is non-inferior to NIV with a margin of 8 percentage points. Linear regression will be used for the confirmatory analysis.

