**Fig. 1 Fig1:**
[figure not shown]
Study flow chart according to the Consolidated Standards of Reporting Trials

For patients randomized to the NIV arm, NIV is initialized using a regular oral/nasal mask. Pressure support will be initiated with 18/4 mbar for adaptation and then increased to achieve effective respiratory support while trying not to lose tolerance.

With both devices, oxygen should be supplemented to reach an O_2_ saturation range of 88–92%. Patients should use respiratory support as long as possible, both day and night. The study intervention can be initiated at the emergency room or in intermediate or intensive care or a specialized respiratory medicine ward as mentioned above. The use of either device does not require alteration to usual care pathways (including use of any medication), and these will continue for both trial arms.

Statistical monitoring based on data in the database will take place at regular intervals and include the verification that reasons for switching devices are documented in a timely manner and follow the protocol specification. It will also be used to ensure that investigators provide the duration of device use as a measure of patient compliance. Departures at the site level from protocol specifications will lead to corrective measures.

Patients are covered by insurance while in the trial and after the trial; treatment is at the physician’s discretion but may include the continued use of the prescribed device.

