### Study endpoints

The primary endpoint is the proportion of patients with treatment failure within 72 h. Treatment failure is defined by (a) switch to another method of non-invasive ventilation or (b) intubation or (c) death.

It is highly recommended that intubation only be initiated if pH < 7.15 and at least one of the following criteria is met: (i) Glasgow Coma Scale (GCS) < 10, (ii) O_2_ saturation < 85% or PaCO_2_ < 45 mmHg despite FiO_2_ > 0.5 and (iii) respiratory rate > 40 cycles/min.

Switching to another method of non-invasive ventilation should only be considered in the following situation:
One of the following criteria is met within 1 h: decrease in pH by at least 0.06, increase in pCO_2_ by at least 10 mmHg, unacceptable decrease in GCS, increase in respiratory rate by at least 20%, insufficient complianceOne of the following criteria is met after 2 h: unacceptable decrease in pH or pCO_2_, clinically unstable compared to last status (beginning at 4 h), insufficient compliance

The most important secondary endpoints are as follows: (a) proportion of patients that fulfil single components of the primary endpoint (i.e. intubation, switch of device or death within 72 h), (b) proportion of patients intubated within 7 days after hospitalization/randomization, (c) overall survival at 28 and 90 days, (d) (invasive) ventilator-free days up to day 28, (e) (invasive) ventilator-free hours until 72 h or until reaching the primary endpoint (whichever comes first), (f) ICU and hospital lengths of stay, (g) proportion of patients requiring sedation and (h) quality of life at day 28 according to St George’s Respiratory Questionnaire (SGRQ) and the Severe Respiratory Insufficiency (SRI) questionnaire, both of which are validated and standard instruments used in patients with obstructive airway diseases [27–29]. Safety issues of interest are device related intolerance/complications and severe diseases acquired under treatment. Compliance and acceptance of devices will also be investigated.

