^d^Standard (long) version of informed consent, if patient is still able to give informed consent

^e^All medications within the last 24 h resp. laboratory parameters any time within the last 24 h

^f^A change of device is possible, if switch criteria are fulfilled OR need for intubation criteria are met before 72 h → primary endpoint reached

^g^Ongoing treatment, if patient still hospitalized

The case report form (CRF) will be designed by the ZKS Leipzig in cooperation with the co-ordinating investigator and provided in electronic form (eCRF). In order to facilitate the documentation as per protocol in case of malfunction of the electronic system or any of its components, a paper version of the CRF (interim CRF) will be provided in the ISF (investigator site file). The data on this paper version will be transferred to the eCRF as soon as the electronic system is available again.

The eCRF must be completed shortly after each trial visit according to ISO 14155:2020 chapter 7.8.1 and to enable central monitoring of the trial data.

Access to the data base will be limited to authorised staff and patients will be identified by patient-ID only. Authorization is granted by the site’s investigator using the trial specific staff signature and delegation log. Based on the staff signature and delegation, log access to the eCRF will be granted by the responsible staff at the ZKS Leipzig. Authorised staff members on site will be able to enter and update data as well as finalise data by electronic signature during the conduct of the trial according to a trial specific concept for documentation. All entries and data changes will be tracked automatically including date, time and person who entered/changed information (audit trail). Major correction(s) or major missing data have to be explained.

Each trial centre is initiated by the clinical monitor before start of the study, which means that the implementation of the study is explained and all necessary documents are provided. During trial conduct, central and statistical monitoring procedures will be combined with on-site monitoring visits in order to achieve high protocol compliance and data quality, as well as to ensure patients’ safety and rights. All clinical data are entered by the investigators (or their designated staff) into electronic data collection forms, which are all available in the database. Access to the data base will be limited to authorised staff only after training on the database.

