The proportion of patients (with 95% confidence limits) who were randomly allocated to NIV therapy but changed to NHF due to insufficient efficacy and avoid an immediate intubation and vice versa will be analysed. Both the proportion with and without later intubation will be provided. Although these NIV-to-NHF proportions are a form of data exploration, useful estimates on the value of NHF as rescue treatment in patients who do not tolerate NIV may be derived, especially if compared to usually reported proportions of intubation immediately initiated after NIV.

The proportion of switches to another device before intubation will also be compared to investigate potentially existing preferences in favour of NIV.

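### Exploratory rescue analysis: proportions defined by switches for insufficient efficacy are not specific to patients who cannot tolerate NIV, and the suggested outside comparison is open to case selection

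*Protocol article*

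**What the plan says.** The last part of the section Sample size and statistical analysis describes an analysis of device switches. It takes patients randomised to NIV who "changed to NHF due to insufficient efficacy and avoid an immediate intubation and vice versa will be analysed", and reports proportions with and without later intubation. It calls these proportions a form of data exploration. It then says that "useful estimates on the value of NHF as rescue treatment in patients who do not tolerate NIV may be derived". The same sentence goes on to recommend an outside benchmark for these estimates: "especially if compared to usually reported proportions of intubation immediately initiated after NIV".

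Other sections bear on who these patients are:

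- **Study endpoints** lists the reasons for switching in two time windows. Within 1 h they include a "decrease in pH by at least 0.06", a rise in pCO2, a fall in GCS, a rise in respiratory rate and, as its own item, insufficient compliance. Compliance is listed again for the window after 2 h.
- **Study endpoints** sets a different threshold for intubation: "It is highly recommended that intubation only be initiated if pH" is below 7.15 and at least one further criterion is met.
- **Abstract, Methods** says that the switch "acts as a rescue treatment in absence of intubation criteria".
- **Table 1, footnote f** says: "A change of device is possible, if switch criteria are fulfilled OR need for intubation criteria are met" before 72 h.
- **Interventions** says that NIV pressure is "increased to achieve effective respiratory support while trying not to lose tolerance", and that statistical monitoring checks the documentation of switch reasons.
- **Discussion** concedes that clinical judgement in switching or intubating cannot be avoided and does not always show in the CRF.

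**The concern.** A patient can leave NIV because gas exchange worsens despite adequate use, or because the mask or pressure is not accepted. These patients may differ in prognosis and in what NHF can offer them. An estimate built on the first kind does not automatically describe the second. NHF after failed tolerance of NIV is a question of real interest here: the Background cites a pilot study in such patients, and the Discussion says that up to 30% do not tolerate NIV.

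The second issue is the suggested benchmark. If switching is intended for patients who do not meet intubation criteria, the switchers' later intubation rate reflects who was chosen for switching as well as anything NHF does. A published proportion from other cohorts, with its own denominator and case mix, cannot separate the two.

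What is at stake is the interpretation of one exploratory result. The confirmatory analysis, its margin and the sample size do not depend on it.

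**Working it through.** The rescue paragraph states no figure, so there is none to reproduce. The check is mainly a comparison of texts, with two short calculations.

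**1. Group counted against group described.**

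- Counted: switches for insufficient efficacy.
- Described: patients who do not tolerate NIV.
- *Literal reading.* Efficacy means the physiological criteria (pH, pCO2, GCS, respiratory rate). A patient switched only for insufficient compliance is then not counted, although that is the listed reason closest to intolerance.
- *Loose reading.* Insufficient efficacy stands for any failure of NIV. The count then includes compliance switches, but pooled with physiological failures.
- Either way, the proportion is not an estimate for intolerant patients. The titration rule in Interventions, which sets effective support against tolerance, shows that the article can treat the two as distinct. It does not itself classify switch reasons.

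**2. Can a switch be indicated while intubation criteria are not met?**

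- Inputs: eligible pH from 7.15 to below 7.35 (Study population); switch criterion of a 0.06 fall within 1 h; recommended intubation only below pH 7.15 plus another criterion (Study endpoints).
- Threshold: 7.15 + 0.06 = 7.21. From any entry pH of 7.21 or more, a fall of exactly 0.06 leaves pH at or above 7.15.
- Example: 7.30 − 0.06 = 7.24, so the switch criterion is met and the pH part of the intubation rule is not.

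Selection is therefore possible under the criteria and agrees with the Abstract's description of rescue. How strict it is remains open. Footnote f can be read as also allowing a change of device once intubation criteria are met, and the intubation thresholds are recommendations. The documents give neither switches by reason nor later-intubation rates, so no size or direction can be attached to the distortion.

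**3. Precision if switches are reported by reason.**

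- Inputs: 680 analysed, 1:1 allocation, 15% failure assumed (Sample size and statistical analysis).
- NIV arm: 680 / 2 = 340. Planned failures: 0.15 × 340 = 51. This caps the number of switchers only at the planning rate.
- Assumptions, not in the documents: reason-specific groups of 10, 16 or 26, and about 30% later intubated.
- Wilson 95% interval, with p = x/n and z = 1.96: [p + z²/(2n) ± z·√(p(1 − p)/n + z²/(4n²))] / (1 + z²/n).

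| Later intubated / switchers | Proportion | 95% interval |
|---|---|---|
| 3/10 | 30.0% | 10.8% to 60.3% |
| 5/16 | 31.2% | 14.2% to 55.6% |
| 8/26 | 30.8% | 16.5% to 50.0% |
| 15/51 (all planned failures are switches) | 29.4% | 18.7% to 43.0% |

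**The case against.** The strongest reply is that the wording is simply loose. The article defines no switch category called insufficient efficacy. Study endpoints puts compliance in the same list as the physiological criteria without sorting them. The Abstract and Background attach an NIV failure rate of 11–34% to poor tolerance, as if the two were one. On that view the paragraph means only that NIV did not work for the patient. This has force: a reader might infer that the wrong group has definitely been specified, and the text supports that only on the literal reading. The mapping of insufficient compliance to intolerance is also not stated in the article. What survives is that the loose reading gives a mixed group, which is still not specific to intolerance.

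A reader might also infer that the comparator is a set of patients who were all intubated, so that any switcher who escapes intubation would look like a success of NHF. The text refers to reported proportions, which have a denominator, so that inference fails. What remains is the ordinary limit of a historical comparison, made sharper by the selective switching rule.

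Finally, the paragraph is hedged, specifies no test or decision rule, and is labelled exploratory. It should not be read as a planned conclusion of the trial. Reporting with and without later intubation is already foreseen, and the Discussion discloses clinical discretion. Tabulation by reason would often be left to the analysis plan. The fault is therefore not a missing table. It is that the paragraph names one group, makes its remark about another, and presents the outside comparison as adding value without a caution about selection.

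**Conclusion.** The point stands as a minor one, confined to an exploratory analysis. As worded, the rescue proportions cannot speak specifically for patients who do not tolerate NIV, whichever way insufficient efficacy is read. The suggested comparison with reported immediate-intubation proportions is non-randomised and subject to case selection, so it cannot be read as a rescue effect of NHF.

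It would go too far to say that the comparison favours NHF, or by how much: that would need switch reasons, later-intubation rates and the case mix of the outside cohorts, none of which the documents give. The selection argument rests on the Abstract's description of rescue, the two sets of thresholds and the conceded clinical discretion. It is weakened, though not removed, if footnote f permits switching after intubation criteria are met. Primary and secondary endpoints are unaffected.

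**What to change.** Reword the rescue paragraph in three respects:

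1. Count switches for any documented reason, in both directions, and report them with and without later intubation by reason: efficacy, compliance/intolerance, both, or unclear.
2. Base any remark about patients who do not tolerate NIV on the compliance/intolerance group alone.
3. Present outside proportions of immediate intubation as descriptive context only, with no inference about a rescue effect.

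The cost is a few sentences. No new data item appears to be needed, since documentation of switch reasons is already monitored. There are two downsides. Some reasons will be unclear in the CRF, hence the separate category. The reason-specific groups will be small, with intervals as wide as those tabulated above, so even the corrected analysis may support only a cautious description.

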### Roles and responsibilities

The Leipzig University as the responsible institution, together with ZKS Leipzig (coordinating centre) and the trial sites, is responsible for the implementation and data processing in accordance with Article 4(7) of the General Data Protection Regulation 2016/679 in this trial. The ZKS Leipzig is responsible for implementation of procedures for data collection, storage, protection, retention and destruction. The data stored in the trial database is secured against unauthorized access.

The study is supervised by a project manager in close cooperation with the coordinating investigators, who takes care of all regulatory and organizational processes and monitors the conduct of the study. In addition, the study team consists of data management, clinical monitoring and biometric staff. The data management team monitors the electronically entered data and makes inquiries to the clinics if necessary. Clinical monitors appointed by ZKS Leipzig visit the recruiting sites regularly and verify the informed consent forms. This serves to verify that the patient has unambiguously given his or her consent for trial participation as well as for data capture, transmission and analysis. The patients are informed of this fact and agree to the procedure with the patient information/informed consent.

There is no trial steering committee.

### Harms

All adverse events will be documented on special AE-forms from start of ventilation until discharge or day 28 (whichever comes first) for each patient. Information relevant to AEs will be solicited by the investigator at every patient’s study visit. In addition, the patient will be asked to inform the clinical trial site of any health problems arising between visits by phone or personal visit. Adverse events are classified by their seriousness, intensity and relationship to the therapeutic intervention.

If an AE fulfils any of the criteria for a SAE, the AE has to be marked as “serious” on the CRF. This applies to all SAEs, whether or not they are considered to be related to the study treatment.

For both serious and non-serious AEs, documentation should be supported by an entry in the patient’s health record. Required information includes the type of AE, seriousness of the event, an estimate of its severity, start date, date of resolution, actions required, outcome and an assessment of its relationship to trial intervention. All abnormal physical and/or laboratory results which are considered to be clinically relevant by the investigator should be recorded as (S)AEs. The investigator will follow-up the event until the AE has been resolved, resolved with sequelae, or was fatal. The investigator should report each AE on according eCRF in a timely manner and continuously during the trial. Within the database, a selection of the radio button “serious” will trigger an automatic e-mail-announcement of the SAE at ZKS Leipzig. If any of the involved ethics committees should require SAE-reports, these will be derived from the trial database at the required intervals. The ELVIS trial follows §23b MPG. Thus, there are no SAE-reporting obligations to the competent authority.

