### Randomization, recruitment and data collection

Randomization will be performed centrally, via a secure web-based tool. The allocation to the intervention arm (randomization ratio 1:1) uses a minimization procedure with a stochastic component that takes into account trial centre, pH ≤/> 7.3 and BMI ≤/> 30 kg/m^2^. The randomization result forwarded automatically via email to the investigator and the Clinical Trial Centre Leipzig.

Adequate recruitment will be encouraged through regular Newsletters including current recruitment status, regular consultations with trial sites by the monitor/coordinating investigator and trial meetings.

The schedule of study visits and list of parameters collected can be found in Table 1. Within the first 24 h, data are collected at 1, 2, 4, 6, 12 and 24 h after which collection takes place at 36, 48 and 72 h. There is a discharge visit and one at day 7 as well as telephone visits on days 28 and 90.

**Table 1 Tab1:** Schedule for study interventions according to Recommendations for Interventional Trials (SPIRIT) indications

Examination/assessment		Treatment											Follow-up		
	Screening	Visit 0	Visit 1						Visit 2		Visit 3		Visit 4	Visit 5^**a**^	Visit 6^**a**^
Timepoint		0 h	1 h ± 30 min	2 h ± 30 min	4 h ± 30 min	6 h ± 30 min	12 h ± 60 min	24 h ± 60 min	36 h ± 90 min	48 h ± 120 min	72 h ± 180 min	discharge	day 7^**b**^ ± 1 day	day 28	day 90
Informed consent	X^c^											X^d^			
Inclusion criteria/exclusion criteria	X														
Randomization		X													
Patient characteristics (anamnesis, comorbidity)	X														
Medication	X							X^e^		X^e^	X^e^	X			
Clinical parameters (heart rate, respiratory rate, blood pressure, Borg’s scale)	X		X	X	X	X	X	X	X	X	X	X	X		
Adverse events/side-effects			X	X	X	X	X	X	X	X	X	X	X	X	X
Glasgow coma scale (GCS)	X		X	X	X	X	X	X	X	X	X	X			
Blood gas analysis (BGA): pO_2_, pCO_2_, pH, SpO_2_, FIO_2_	X		X	X	X	X	X	X	X	X	X	X	X		
Therapy according to allocated device: device parameters		X	X^6^	X	X	X	X	X	X	X	X	X	X^g^	X^f^	X^f^
Therapy: oxygen supplement		X	X	X	X	X	X	X	X	X	X	X	X^f^	X^f^	X^f^
infection parameters and biomarkers (optional)	X							X^e^			X^e^				

^a^Visits 5 and 6 are conducted by telephone

^b^Assessment of intubation; not applicable, if patient is already discharged since no intubation can be stated in this care

^c^Standard (long) version of informed consent OR concise (short) version of informed consent

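### The Harms text ends adverse event recording at discharge or day 28, while Table 1 schedules it at the day 28 and day 90 calls; the text's window also depends on length of stay, which is compared between arms

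*Protocol article*

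**What the plan says.** The Harms section of the protocol article sets the period for documenting all adverse events as "from start of ventilation until discharge or day 28 (whichever comes first"). The same paragraph then states: "Information relevant to AEs will be solicited by the investigator at every patient’s study visit". It also asks patients to tell the site about "any health problems arising between visits by phone or personal visit".

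The section Randomization, recruitment and data collection lists the visits after the 72 h assessment: "There is a discharge visit and one at day 7 as well as telephone visits on days 28 and 90". A footnote to Table 1 adds: "Visits 5 and 6 are conducted by telephone". In that table the row "Adverse events/side-effects" is marked at every time point from 1 h to 72 h, at discharge, and at days 7, 28 and 90. The marks in this row carry no footnote. The day 7 column heading has one, which concerns the intubation assessment and says "not applicable, if patient is already discharged".

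The Study endpoints section makes ICU and hospital length of stay a secondary endpoint. The safety interests it names are intolerance and complications related to the device, and severe illness acquired during treatment.

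**The concern.** The text and the table give different end points for AE recording, and a site cannot settle the matter from the article. Take a patient discharged on day 8 who develops pneumonia on day 15. The documentation rule leaves the event out. The table, and the instruction to ask at every visit, bring it in at the day 28 call.

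The second issue is what the text rule does to the comparison if it is followed. Each patient is then observed for AEs only while in hospital. Hospital stay is something the trial compares between arms, so the length of the safety window is itself an outcome. If one device leads to earlier discharge, its patients are watched for fewer days and fewer of them will have a recorded event, even when the daily risk is the same. At stake is the harms comparison, which matters in an open-label trial that proposes one device as an alternative to the other.

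**Working it through.** The plan states no figure on this point, so there is none to reproduce. The check sets the passages side by side and then sizes the consequence with assumed inputs.

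**Step 1: the table row.** Table 1 has 15 time columns: screening, 0 h, nine from 1 h to 72 h, discharge, day 7, day 28 and day 90. The AE row is blank at screening and 0 h and marked in the other 13.

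**Step 2: each mark against the text's window.**

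| Marked time point | Inside the Harms window? |
|---|---|
| 1 h to 72 h, discharge | Yes, up to discharge |
| Day 7 | Yes if still in hospital; no if discharged |
| Day 28 (telephone) | No for every patient already discharged |
| Day 90 (telephone) | No for every patient |

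The longest window that the text allows is 28 days; the table runs to 90.

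**Step 3: effect of a window that ends at discharge.** The document gives neither lengths of stay nor AE rates, so all inputs here are assumptions: the same constant AE rate r per day in both arms, all patients in an arm staying T days, and events following a Poisson process.

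- Ratio of expected AE counts = T2 / T1.
- Share of patients with at least one AE = 1 − exp(−r × T).

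With r = 0.05 per day:

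| Stays (days) | Count ratio | Share with an AE |
|---|---|---|
| 8 vs 9 | 9/8 = 1.125 | 33.0% vs 36.2% |
| 8 vs 10 | 10/8 = 1.25 | 33.0% vs 39.3% |
| 7 vs 10 | 10/7 = 1.43 | 29.5% vs 39.3% |

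For 8 vs 10 days: 1 − exp(−0.4) = 0.330 and 1 − exp(−0.5) = 0.393, a gap of about 6 percentage points with no true difference in rate.

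**Step 4: a fixed window.** Over 28 days in both arms, 1 − exp(−0.05 × 28) = 1 − exp(−1.4) = 0.753, so 75.3% in each arm and no spurious gap.

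**The case against.** The strongest reply is that text and table can be reconciled. The Harms section also requires the investigator to follow each event to its outcome, which needs contact after discharge. The later marks could then mean follow-up of open events only, with new events recorded to discharge. This is a possible reading and softens the conflict. It does not remove it: the table does not restrict the marks, and the Harms section has AEs solicited at every visit and invites reports of newly arising problems.

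A related reply is that the table's footnotes look unreliable. One marker matches no footnote, and a note about changing device before 72 h sits on day 28 and day 90 cells. That weakens inferences from footnotes, but the AE marks are plain and the day 90 column is clear.

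It can also be argued that an inpatient window suits safety interests tied to the device and to the treatment period, that survival to day 90 is captured separately, and that an analysis plan could handle unequal exposure. These points limit the damage. They do not say which window applies.

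A reader might infer more than the documents support:

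- **Day 7 is a further contradiction.** It fits the text for patients still in hospital, and the column's footnote partly allows for discharge.
- **Sites will use different windows.** They may, but there is one centrally designed eCRF with central monitoring, and the full protocol, which is not shown, may impose one rule.
- **Events between randomisation and the start of ventilation are lost.** The Interventions section has devices started immediately, so any such gap is negligible.

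**Conclusion.** The inconsistency is real and in the current text. It is clear at day 90 for every patient and at day 28 for every patient already discharged.

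The consequence for the harms comparison is conditional. It needs the text rule to be followed, stay to differ between arms, and AEs to be compared as simple proportions or counts. The document shows none of these as fact; it supports a difference in stay only by making length of stay a between-arm endpoint. The gap of 33% versus 39% illustrates the mechanism and does not forecast its size. It rests on an assumed constant rate of 0.05 per day and stays of 8 versus 10 days, and would be smaller if events cluster in the first days.

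It would be wrong to infer that the main result is at risk. The primary endpoint is fixed at 72 h, and neither it nor the sample size uses the AE window. This point should be corrected for the safety reporting and for the data that the monitoring board reviews.

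**What to change.** Bring the Harms section and Table 1 to one AE window that is the same for every patient, for example randomisation to day 28 regardless of discharge, with the existing day 28 call collecting events after discharge. State what the day 90 call records: new events, serious events only, or follow-up of open events. Add a matching footnote to the AE row and align the eCRF. Compare AEs between arms over that common window.

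If collection can no longer change, report AEs per day at risk. This is a partial repair: it adjusts for unequal observation time, but events after discharge stay unseen.

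The cost is a protocol clarification, an eCRF adjustment and a few more AE entries per patient. No new contact is needed, since the plan already includes "telephone visits on days 28 and 90". The drawback is that events after discharge would be self-reported by telephone and so less well documented than those seen in hospital.
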